## Abstract

The progressive nature of heart failure (HF) coupled with high mortality and poor quality-of-life (QoL) mandates greater attention to palliative care (PC) as a routine component of HF management. Limited evidence exists from randomized controlled trials supporting the use of interdisciplinary palliative care in the progressive course of HF. The early palliative care in heart failure trial (EPCHF) is a prospective, controlled, nonblinded, multicenter study of an interdisciplinary palliative care intervention in 200 patients with symptomatic HF characterized by NYHA ≥ 2. The 12-month EPCHF intervention includes monthly consultations by a palliative care team focusing on physical and psychosocial symptom relief, attention to spiritual concerns and advance care planning. The primary endpoint is evaluated by health-related QoL questionnaires after 12 months of treatment. First the functional assessment of chronic illness therapy palliative care (FACIT-Pal) score evaluating QoL living with a chronic disease and second the Kansas City cardiomyopathy questionnaire (KCCQ) measuring QoL living with heart failure will be determined. Secondary endpoints are changes in anxiety/depression (HADS), symptom burden score (MIDOS), spiritual well-being functional assessment of chronic illness therapy spiritual well-being scale (FACIT-Sp), medical resource and cost assessment. EPCHF will help evaluate the efficacy and cost-effectiveness of palliative care in symptomatic HF using a patient-centered outcome as well as clinical and economic endpoints. EPCHF is funded by the Bundesministerium für Bildung und Forschung (BMBF, 01GY17).

## Background and rationale

The epidemiological burden of heart failure (HF) is tremendous, with an estimated 26 million people affected worldwide [1]. HF currently affects over 2 million patients in Germany. Accordingly, HF was the most common cause of disease-related hospitalization, the second leading cause of hospital stay, and the leading cause of in-hospital deaths in Germany in 2013 [1]. Despite recent therapeutic advances, HF is a debilitating syndrome that results in a high burden of symptoms and poor QoL. Patients suffer not only from physical effects but also from psychosocial and spiritual distress [2, 3]. Selected HF patients are candidates for aggressive treatments, such as cardiac transplantation or mechanical circulatory support; nevertheless, the application of these therapies to the broader HF population is limited by constrained resources [4]. The progressive nature of HF coupled with high mortality rates and poor QoL mandates greater attention to palliative care (PC) as a routine component of HF management [5].

PC with its focus on management of symptoms, psychosocial support, and assistance with decision making has the potential to improve the quality of care and reduce the use of medical services [3, 4]. However, PC has traditionally been delivered late in the course of disease to patients who are hospitalized in specialized inpatient units or as a consultative service for patients with uncontrolled symptoms [5, 6]. Previous studies have suggested that late referrals to palliative care are inadequate to alter the quality and delivery of care provided to patients [7, 8]. To have a meaningful effect on patients’ QoL and end-of-life care, PC services should be provided earlier in the course of the disease. We here postulate that introducing of PC earlier is feasible and beneficial among patients with symptomatic HF in the outpatient setting.

PC is a multidisciplinary approach that focuses on providing patients with relief from symptoms, pain, and stress of living with a serious illness at any stage of disease [6]. The goal of the current study is to examine the effect of early integration of PC within standard cardiac care on QoL, reported cardiac outcomes, and the use of health services among HF patients.

We hypothesized that patients who received early PC in the ambulatory care setting, as compared with patients who received standard cardiac care alone, would have a better QoL due to lower rates of depressive symptoms, symptom burden, unmet spiritual needs, reported cardiac outcomes and less aggressive end-of-life care thereby improving QoL for both, patients and their caregivers.

Despite consensus-panel and guideline recommendations the integration of PC with evidence-based HF therapies in the later stages of disease is limited [9, 10]. Many physicians equate PC with end-of-life care and prognostic uncertainty poses a challenge in choosing the appropriate time point to implement PC. Furthermore, cardiologists typically lack formalized training in the PC-principles and it is less clear which HF patients benefit from palliative interventions and which interventions improve QoL achieving outcomes desired by patients and family members [9]. However, multiple recent pilot studies in HF populations have suggested that PC may reduce symptom burden and improve QoL [11–13]. These studies have highlighted the importance of symptoms, such as anxiety and depression in HF patients in addition to the commonly recognized symptoms of fatigue, dyspnea and nausea. Moreover, a randomized trial of PC in Stage 4 lung cancer showed improved patient’s symptoms, improves QoL and patients randomized to PC survived longer than those randomized to usual care [14]. Furthermore, multiple studies in oncology and noncancer illness patients have shown reduced costs leading to increased interest of whether similar results can be found in other common diseases, such as HF [15–17]. These studies provide the foundation and rationale for a large-scale randomized HF trial sufficiently powered to assess the effect of early palliative care on clinical outcomes in HF patients.

To help create this body of evidence, the BMBF has funded the early palliative care in heart failure trial (EPCHF) to evaluate if a multidimensional palliative care intervention improves health-related outcomes relative to usual care alone in symptomatic HF patients (Registration No.: DRKS Register 00013922, Studiencode: MED2-201604_EPCHF, Sponsor: BMBF FKZ: 01GY1704). This article describes the design and rationale of the EPCHF trial (https://www.gesundheitsforschung-bmbf.de/de/epchf-studie-fruhe-palliativmedizinische-intervention-bei-patientinnen-und-patienten-mit-7630.php). The authors are solely responsible for the design and conduct of this study, the drafting and editing of this paper and its final contents. Of note, the BMBF is currently funding multiple clinical trials and research projects related to palliative care (see https://www.bmbf.de).

## Methods

### Trial design

EPCHF is a prospective, controlled, two-arm, non-blinded, randomized, multicenter clinical trial of early palliative care integrated with standard cardiac care, as compared with standard cardiac care alone (Fig. 1). The multicenter study will be performed at the departments of Internal Medicine and Palliative Care of the University Hospital of Bonn and departments of Internal Medicine and Palliative Care of the University Hospital of Düsseldorf. Eligible patients with symptomatic HF and dyspnea NYHA ≥ 2 will be randomly assigned to one of the two groups in a 1:1 ratio to usual contemporary HF care or usual care combined with the EPCHF intervention (Fig. 1). Subjects are assigned treatment using a complete randomization scheme. Patients who are assigned to early PC will meet with a member of the PC team, which consisted of board-certified PC physicians and advanced-practice nurses within the time of hospitalization after enrollment and at least monthly thereafter in the outpatient setting during the 12 months of follow-up (Figs. 2 and 3). The palliative care intervention focuses on symptom relief, attention to spiritual concerns, and advance care planning. The trial is non-blinded, since it is not possible to execute a double-blinded trial of the EPCHF intervention given that the intervention involves a multidisciplinary team. The duration of the intervention is 12 months, but patients in both groups are followed until death or the end of the study (~ 3.5 years). The primary endpoint refers to health-related QoL after 12-month follow-up (Fig. 3).

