### Study population

The study will enroll patients with symptomatic HF defined by dyspnea NYHA ≥ 2. Inclusion and exclusion criteria are presented in Tables 1 and 2. Mortality risk due to HF will be calculated by the Seattle Heart Failure Score [18].

**Table 1 Tab1:** Inclusion criteria

Inclusion criteria	Subjects will only be included in the study if they meet all of the following criteria
	Age ≥ 18 years
	NYHA class II–IV symptoms (suspected cardiac dyspnea)
	Systolic HF with a LVEF ≤ 35% or HF with preserved ejection fraction (NYHA class II–IV, elevated natriuretic peptides (NP), left ventricular hypertrophy (LVH) or left atrial enlargement (LAE) or diastolic dysfunction
	BNP ≥ 100 pg/mL or NT proBNP ≥ 400 pg/mL
	Subjects with the ability to follow study instructions and likely to attend and complete all required visits
	Written informed consent

**Table 2 Tab2:** Exclusion criteria

Exclusion criteria	Subjects will not be included in the study if any of the following criteria applies
	Inability to read, understand and respond to question in German
	Previous consultations of palliative care services
	Patients in intensive care unit, on a ventilator, pre- or post-heart transplant
	Non-cardiac terminal illness
	Women who are pregnant or planning to become pregnant, nursing women
	Simultaneously participation in another study or participation in any study involving administration of an investigational medicinal product within 30 days prior to study beginning
	Subjects with a physical or psychiatric condition which at the investigator’s discretion may put the subject at risk, may confound the trial results, or may interfere with the subject’s participation in the study
	Known or persistent abuser of medication, drugs or alcohol

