### Statistical analysis

Primary endpoints: the two primary endpoints will be tested in a two-step procedure. In the first step the hypothesis of equal scores for the FACIT-Pal in the two treatment groups will be tested with a two-side *t* test at a level of 5%. In case of the rejection of the null-hypothesis in the first step, the second hypothesis of equal KCCQ-scores in the two treatment groups will be tested again with a two-sided *t* test at the level of 5%. This test procedure controls a family wise error rate of 5%.

A comparably high number of drop-outs (~ 20%) especially due deaths are to be expected. Since this kind of censoring is definitely correlated to the QoL-measurement, the results for the QoL-score might be biased. An optimal choice of a procedure for the replacement of missing values would require a detailed knowledge about this correlation, which is not available. Missing values will not be replaced for the primary analysis of the two primary outcome variables. A sensitivity analysis will be performed replacing missing values by the last observation carried forward method.

For both variables the course of QoL scores over the observational time will analyzed descriptively by fitting mixed linear models to the data. 95%-confidence interval will be estimated for the score values separated by treatment groups and for measurement times. A second identical analysis for the primary endpoint will be performed based on the per-protocol population (PP), which is defined as the patients treated and observed according to protocol. This analysis will only be performed if ITT and PP-population differ.

Secondary endpoints: the secondary endpoints will be analyzed descriptively in the intention-to-treat collective.

Psychosocial symptoms: patients are screened for symptoms of anxiety and depression using the Hospital Anxiety and Depression Scale (HADS). The HADS has been widely used in studies as a psychologic screening test for the states of anxiety and depression. Patients who screen positive for either anxiety or depression receive a more thorough assessment and management as specified by a treatment algorithm used to determine the need for a mental health referral and the possible use of antidepressants, anxiolytics, stress management techniques, and psychotherapy.

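### The primary t tests leave out centre, heart failure phenotype and baseline score, so chance imbalance under complete randomisation goes uncorrected, at a modest cost in precision

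*Protocol article*

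**What the plan says.** Under Trial design, patients are "randomly assigned to one of the two groups in a 1:1 ratio", and the method is named: "Subjects are assigned treatment using a complete randomization scheme". In standard usage this means no blocks, strata or minimisation, and the article names no stratification factor. The sites are the Bonn hospital and the "departments of Internal Medicine and Palliative Care of the University Hospital of Düsseldorf".

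Under Study population, Table 1 admits two phenotypes: "Systolic HF with a LVEF ≤ 35% or HF with preserved ejection fraction". The Abstract gives the size: an "interdisciplinary palliative care intervention in 200 patients with symptomatic HF".

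Under Statistical analysis, the "hypothesis of equal scores for the FACIT-Pal in the two treatment groups will be tested with a two-side" t test at 5%. KCCQ follows in the same way if the first test rejects. No covariate is named. The mixed linear models for these two scores are described as descriptive, with results by treatment group and time. The section expects roughly 20% drop-out and does not replace missing values in the primary analysis. It closes by leaving further analysis details to a statistical analysis plan. Under Data collection, the baseline questionnaires are completed before randomisation.

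**The concern.** Centre and phenotype are both known at enrolment, and both could plausibly be related to quality of life at 12 months. Each hospital contributes its own cardiology and palliative care departments, and the two phenotypes are different patient groups. With about 100 patients per arm and unrestricted allocation, the arms can differ noticeably on either factor. A t test of the two group means then attributes any resulting difference in score to treatment.

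Two things are at stake. One is precision: variation explained by known baseline factors stays in the error term. The other is how a realised imbalance is read. The trial is non-blinded with patient-reported primary endpoints, so a visible baseline difference invites a challenge that the stated primary analysis cannot answer.

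**Working it through.** **Inputs from the article.** N = 200 at 1:1, about 100 per arm; about 20% drop-out, leaving about 80 per arm analysed; two-sided 5% tests in fixed sequence. The sequence does control the family-wise rate at 5%. The article gives no planning effect, SD or power, so N = 200 itself cannot be reproduced.

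**Assumptions (not in the article).** Each factor is present in 20 to 50% of patients for the imbalance figures. Each shifts the score by 0.3 to 0.5 residual SD. For power, the treatment effect is 0.45 SD, close to the difference detectable with 80% power at 80 per arm: (1.960 + 0.842) × √(2/80) = 0.44.

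**1. How large can imbalance be?** The between-arm difference in prevalence has SD √(2p(1−p)/n).
- n = 100, p = 0.5: SD 0.0707, 95% range ±13.9 points; P(10 points or more) = 15.7%.
- n = 100, p = 0.3: SD 0.0648, ±12.7 points; 12.3%.
- n = 100, p = 0.2: SD 0.0566, ±11.1 points; 7.7%.
- n = 80 (analysed set), p = 0.5: SD √(0.5/80) = 0.0791; 0.10/0.0791 = 1.26, so about 21%.

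Arm sizes matter little. A split of 86:114 or worse has probability 5.6%, but changes the variance factor only from 1/100 + 1/100 = 0.0200 to 1/86 + 1/114 = 0.0204.

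**2. What does imbalance do to the estimate?** Shift = imbalance × factor effect. At 10 points it is 0.10 × 0.3 = 0.03 SD to 0.10 × 0.5 = 0.05 SD. The standard error with 80 per arm is √(2/80) = 0.158 SD.

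**3. Error rate.** Averaged over randomisations, the unadjusted t test under complete randomisation gave a simulated type I error of 4.9 to 5.2%. Given a realised phenotype imbalance (80 per arm, factor effect 0.3 to 0.5 SD) it was:
- 5.0 to 5.5% at 10 points;
- 5.8 to 6.7% at 15 points;
- 6.3 to 8.7% at 20 points. At p = 0.5 a gap this large has probability of only about 1% (0.20/0.0791 = 2.53).

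**4. Power.** Simulated with 160 analysed, treatment effect 0.45 SD, phenotype split 50:50, 10,000 runs per cell:

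| Effect of each factor | Centre split | Complete, t test | Complete, adjusted | Stratified, adjusted |
|---|---|---|---|---|
| 0.3 SD | 50:50 | 78.5% | 79.8% | 81.2% |
| 0.3 SD | 70:30 | 79.0% | 80.1% | 80.3% |
| 0.5 SD | 50:50 | 75.4% | 79.5% | 80.9% |
| 0.5 SD | 70:30 | 75.5% | 79.3% | 81.3% |

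The Monte Carlo standard error of each figure is about 0.4 points.

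An analytic check agrees. With both factors at 50%, the t test works with variance 1 + 2 × b² × 0.25, which is 1.045 at b = 0.3 and 1.125 at b = 0.5. Power is Φ(0.45/√(2V/80) − 1.96): 79.5% and 76.5%, against 81.2% at V = 1. The loss is 1.7 and 4.7 points.

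Adjustment alone recovers about 1 point at 0.3 SD and about 4 at 0.5 SD. Stratifying as well adds 0.2 to 2.0 points, on average a little over one. Stratifying while keeping the unadjusted t test made that test conservative (type I error 3.6 to 4.4%).

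**The case against.** The strongest reply is that nothing here is wrong. Complete randomisation followed by a t test is coherent and valid, and in a non-blinded trial it has the advantage that earlier assignments do not reveal the next one. Small blocks within two centres and two phenotypes can be partly guessed. This stands, and it is why the allocation scheme is not the target of the point.

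A reader might infer that complete randomisation is itself a defect, or that the primary result would be biased or tested above 5%. The documents do not support either. The level holds on average, and the added variance (0.5² × 0.25 = 6.25% for one factor worth 0.5 SD at 50% prevalence) belongs to the unadjusted test: the t test carries it even with perfectly balanced arms. Nor would stratification settle differences in delivery between the two palliative care teams, which is a question of treatment-by-centre interaction.

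It can also be said that the analysis plan may add covariates, or that the full protocol may describe strata. The article leaves only further details to that plan, and its primary test is already stated; a covariate model would replace that test. The reading of complete as unrestricted is the usual one, but the authors should confirm it.

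Finally, the size depends on effects and splits that the article does not give. That also stands, so ranges are shown. At the lower end the gain is small.

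**Conclusion.** The point holds for the analysis. The stated primary tests ignore baseline information that the trial already has, under an allocation method that does not limit imbalance in it. The cost is modest: about 1 to 2 power points if centre and phenotype are each worth 0.3 SD, and about 4 to 6 at 0.5 SD, where the upper figure includes stratified allocation. A 10-point imbalance moves the estimate by 0.03 to 0.05 SD, well inside one standard error.

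These sizes rest on the assumed factor effects, a 0.45 SD treatment effect, 80 analysed per arm and the splits shown. They leave out any gain from the baseline score, which would cut residual variance by the factor 1 − r² for a baseline-to-12-month correlation r that the article does not give. This is a matter of precision and conditional bias. It is not a threat to validity, and not a case against complete randomisation.

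**What to change.** Keep the allocation scheme. Before the data are analysed, replace each t test in the fixed sequence with a linear model (ANCOVA) of the 12-month score on treatment, centre, phenotype (LVEF ≤ 35% versus preserved, by the inclusion criterion met at entry) and the baseline value of the same score. Test the treatment coefficient two-sided at 5%, FACIT-Pal first and then KCCQ, so the family-wise rate is controlled as now. Report the unadjusted t test as a sensitivity analysis. State in one sentence what complete randomisation means here.

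The cost is a few lines in the analysis section and no new data: centre and phenotype are known at enrolment, and baseline scores are collected before randomisation.

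Stratified allocation by centre and phenotype is optional and could apply only to patients not yet randomised. The trial-flow figure plans the first patient for April 2018 with 26 months of recruitment, and the Goals of care section describes patient contact in the past tense, so allocation may be well advanced. If it is adopted, use concealed blocks of varying size and keep the strata in the model. The gain of about one power point has to be weighed against greater predictability in an open-label trial.

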**Fig. 1 Fig1:**
[figure not shown]
Intervention scheme of EPCHF. Experimental intervention: additional palliative care to standard cardiac care. The intervention includes monthly consultations by a palliative care team over 12 months (palliative care assessment of physical, psychological, social and spiritual needs, establishing goals of care, assisting with decision making) in the outpatient or inpatient setting. Control intervention: standard cardiac care with palliative care on demand only. Duration of intervention per patient: 12 months. Time of data collection: at baseline and at 4 follow-up visits every 3 months within 12 months

**Fig. 2 Fig2:**
[figure not shown]
Trial flow of EPCHF. The individual treatment duration is 12 months. Trial duration: recruiting period: 26 months. Planned start date (FPFV): 01.04.2018. Planned end date (LPLV): 31.07.2021. Time for preparation of the trial (months): 3 months. First patient in to last patient out (months): 38 months. Time for data clearance and analysis (months): 3 months. Duration of the entire trial (months): 42 months

**Fig. 3 Fig3:**
[figure not shown]
Schedule of activities. Red font: best supportive cardiac care (BSCC). Blue font: additional early integration of palliative care (EIPC). Black font: conducted investigations. ^1^LVEF, LV diastolic dysfunction, hemodynamic, ^2^incl. negative blood pregnancy test for women of childbearing potential

### Study population

The study will enroll patients with symptomatic HF defined by dyspnea NYHA ≥ 2. Inclusion and exclusion criteria are presented in Tables 1 and 2. Mortality risk due to HF will be calculated by the Seattle Heart Failure Score [18].

**Table 1 Tab1:** Inclusion criteria

Inclusion criteria	Subjects will only be included in the study if they meet all of the following criteria
	Age ≥ 18 years
	NYHA class II–IV symptoms (suspected cardiac dyspnea)
	Systolic HF with a LVEF ≤ 35% or HF with preserved ejection fraction (NYHA class II–IV, elevated natriuretic peptides (NP), left ventricular hypertrophy (LVH) or left atrial enlargement (LAE) or diastolic dysfunction
	BNP ≥ 100 pg/mL or NT proBNP ≥ 400 pg/mL
	Subjects with the ability to follow study instructions and likely to attend and complete all required visits
	Written informed consent

**Table 2 Tab2:** Exclusion criteria

Exclusion criteria	Subjects will not be included in the study if any of the following criteria applies
	Inability to read, understand and respond to question in German
	Previous consultations of palliative care services
	Patients in intensive care unit, on a ventilator, pre- or post-heart transplant
	Non-cardiac terminal illness
	Women who are pregnant or planning to become pregnant, nursing women
	Simultaneously participation in another study or participation in any study involving administration of an investigational medicinal product within 30 days prior to study beginning
	Subjects with a physical or psychiatric condition which at the investigator’s discretion may put the subject at risk, may confound the trial results, or may interfere with the subject’s participation in the study
	Known or persistent abuser of medication, drugs or alcohol

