Spiritual concerns: the EPCHF-HF NP completes a spiritual assessment at the time of patient enrolment or at the first outpatient visit after hospitalization using the FACIT-Sp. The NP shares information gathered in the spiritual assessment with the EPCHF team and addresses specific spiritual concerns as appropriate. If needed, the NP arranges for subsequent visits to address concerns raised during the initial assessment.

Moreover, qualitative interview data will supplement the results of questionnaires and gain information about the impact of gender issues and social inequality (e.g., patients with migrant background within the study). In addition, public health researcher with special expertise in the area of health inequality research will analyze the issue between over-indebtedness and HF. Because of the expected relevance of variables pertaining to socioeconomic status and migration background for HF-related outcomes including psychosocial aspects/issues, a careful evaluation of the associations between primary and secondary endpoints and these variables will be investigated.

The secondary endpoints HADS-D, MIDO, FACIT-Sp will be analyzed for differences between the treatment groups by fitting mixed linear models to the data. 95%-confidence interval will be estimated for the score values separated by treatment groups and for measurement times.

The survival times will be compared between the treatment groups by a log-rank test. Cox-proportional hazard models will be used to further explore the impact of the treatment on the survival of the patients.

The frequency of adverse events will be counted in absolute and relative frequencies, separated by treatment groups and depending on severity and relationship to the therapy.

Further details of the analyses for primary and secondary outcomes will be specified in a statistical analysis plan.

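### A baseline mortality-risk score is planned but named in no analysis; the survival hazard ratio could be adjusted for it at almost no cost (low priority)

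*Protocol article*

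**What the plan says.** The score appears once in the protocol article, under Study population: "Mortality risk due to HF will be calculated by the Seattle Heart Failure Score". It is not an eligibility criterion in Tables 1 and 2, and the Statistical analysis section does not name it.

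For survival, the Statistical analysis section gives two sentences: "The survival times will be compared between the treatment groups by a log-rank test", and then "Cox-proportional hazard models will be used to further explore the impact of the treatment on the survival of the patients". No covariates are listed. The same section treats secondary endpoints as descriptive and leaves further detail to a statistical analysis plan.

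Under Trial design, patients are "randomly assigned to one of the two groups in a 1:1 ratio" and "Subjects are assigned treatment using a complete randomization scheme"; no stratification is stated. Survival follow-up is open-ended: "patients in both groups are followed until death or the end of the study". The Abstract gives the size as an "interdisciplinary palliative care intervention in 200 patients with symptomatic HF".

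**The concern.** Eligibility runs from NYHA II to IV and takes in both an ejection fraction of at most 35% and preserved ejection fraction, so baseline mortality risk should vary a good deal between patients. Nothing stated in the randomisation balances that risk, and the stated survival test does not use it. If the score is prognostic, an unadjusted comparison leaves explainable variation in the error. The one estimate the trial obtains can also carry an uneven draw of high-risk patients.

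The trial is non-blinded, and the article leaves the Cox covariates open. If they were settled only after the data had been seen, the reported hazard ratio would be open to selection. Naming the score in advance removes that freedom and uses a quantity the protocol already intends to calculate.

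**Working it through.** The document gives no hazard ratio, death count or power for survival, so there is no stated figure to reproduce. What follows shows sizes under stated assumptions.

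**Inputs from the document.** N = 200 at 1:1, taken as 100 per arm. Recruitment lasts 26 months, and first patient in to last patient out is 38 months (Fig. 2 caption), so survival follow-up runs from 38 − 26 = 12 months to 38 months. The only figure touching on mortality is "A comparably high number of drop-outs (~ 20%) especially due deaths are to be expected". It concerns missing quality-of-life scores; no total for deaths over the full follow-up is given.

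**Assumptions.** Two-sided 5% for survival; conditional treatment hazard ratio 0.6; deaths in 20%, 30% or 40% of patients (40, 60 or 80 deaths); a standardised score with slope 0.3 to 1.0 log-hazard per SD.

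**1. Chance imbalance.** The SD of the standardised difference between arms is √(1/100 + 1/100) = 0.141. P(|difference| ≥ 0.2) = 2 × [1 − Φ(0.2/0.141)] = 0.157, about 16%. A difference of exactly 0.2 SD moves the realised hazard ratio by a factor of about exp(0.2 × slope):

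| Slope per SD | Factor |
|---|---|
| 0.3 | 1.06 |
| 0.5 | 1.11 |
| 0.8 | 1.17 |
| 1.0 | 1.22 |

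For scale, the standard error of the log hazard ratio is about √(4/deaths): 0.32 at 40 deaths, 0.26 at 60 and 0.22 at 80. Even at slope 1.0 the shift of 0.2 is less than one standard error.

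**2. Power with and without the score.** Simulation of 1,500 trials per cell, follow-up uniform over 12 to 38 months, unadjusted versus score-adjusted Cox model:

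| Deaths | Slope 0.5 | Slope 0.8 | Slope 1.0 |
|---|---|---|---|
| 20% | 32% vs 34% | 31% vs 35% | 31% vs 37% |
| 30% | 46% vs 49% | 39% vs 50% | 36% vs 47% |
| 40% | 56% vs 62% | 47% vs 63% | 44% vs 61% |

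The simulation error of one power value is at most √(0.5 × 0.5/1500) = 1.3 points. A separate simulation that also included slope 0.3 gave gains of about 0–8 points at 20% deaths, 2–11 at 30% and 2–19 at 40%.

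**3. A less favourable setting.** With about 20% control-arm deaths (about 33 deaths in all at hazard ratio 0.6) and 2,000 trials per cell, log-rank versus adjusted Cox power was 29.1% vs 29.1%, 28.3% vs 28.8% and 25.5% vs 29.4% for score hazard ratios of 1.5, 2.0 and 2.7 per SD. At treatment hazard ratio 0.5 it was 44.7% vs 43.0%, 45.0% vs 45.2% and 39.9% vs 45.3%. With few deaths the gain is near zero unless the score is very strongly prognostic.

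**4. Validity.** With no treatment effect, the log-rank test rejected in 4.5% to 4.8% of those simulated trials and the adjusted Cox model in 4.4% to 5.1%. Both hold their level.

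**5. Deaths matter more.** Schoenfeld's formula gives 4 × (1.960 + 0.842)² / (ln 0.6)² = 121 deaths for 80% power at hazard ratio 0.6. With 40, 60 and 80 deaths the power is 37%, 51% and 63%. Adjustment does not close that gap.

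**The case against.** The strongest reply is that the plan contains no error. A log-rank test followed by Cox models is standard, and Cox models meant for further exploration are a natural home for covariates. The article sends further detail to an analysis plan that is not shown, and a covariate list is the kind of detail that belongs there. Survival is exploratory: the primary endpoints are the two quality-of-life scores, death is listed only inside a secondary composite, and no power is claimed for it. Chance imbalance of the size shown can arise in any baseline variable of an unstratified trial of 200, and a valid confidence interval already allows for it.

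Most of this stands, and it sets the priority. A reader might infer three stronger things that the document does not support:

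- **That the score enters no analysis.** The article names it in none, but it does not exclude it from the Cox models, and the analysis plan may include it.
- **That the unadjusted hazard ratio is biased.** In simulation with a conditional hazard ratio of 0.60 and slope 1.0, the unadjusted value averages about 0.65. This is non-collapsibility: the marginal and conditional hazard ratios answer different questions, and neither is wrong.
- **That the score is certain to be available for every patient.** The article says only that it will be calculated, and the schedule of activities is a figure that cannot be seen here.

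What the reply does not remove is that the article does settle on one between-arm survival test, and that test is unadjusted. Adjusting for a risk measure already planned is a better use of the same data.

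**Conclusion.** The point holds as a low-priority improvement, not as a flaw that threatens the trial. The article plans a mortality-risk score, ties it to no analysis, and states an unadjusted survival test under randomisation without stated strata. The cost of leaving this as it is ranges from about 0 to 19 points of power, plus a roughly 16% chance of a score difference of at least 0.2 SD between arms. The upper end needs both 40% deaths and a slope near 1.0; with 20% deaths or a weakly prognostic score the loss is a few points or none. The hazard ratio, death fractions and slopes are all assumptions. The log-rank test keeps its type I error, and the two primary t tests are untouched.

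**What to change.** Add one sentence to the Statistical analysis section or the analysis plan, before survival data are compared by arm: the reported survival effect is the hazard ratio with 95% CI from a Cox model containing treatment and the baseline Seattle Heart Failure Score as a continuous covariate, and the log-rank test is reported beside it as the unadjusted comparison. Add that the adjusted hazard ratio is conditional on the score, so that the two results are not read as estimates of the same quantity. Confirm that the score is calculated from baseline data in all randomised patients.

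The cost is that sentence and one extra model term. The score is already planned, type I error stays near 5%, and nothing changes for patients, the sample size or the primary analysis.
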